### Inclusion criteria

A total of 900 children will be recruited for the study. All eligible children within a school will be included and assigned to the same study arm. Youth will be eligible if they are: (1) in upper primary 5–7 (10–14 years) meeting criteria for oppositional defiant disorder or conduct disorder and willing to assent; (2) adult caregiver of the child willing to consent and available for research and intervention activities. A child will be excluded from participation in the study if they are; (1) unable to understand study procedures and participant rights as assessed during informed consent/assent process with the child or parent; (2) if the child or adult caregiver presents with emergency needs (e.g., hospitalization), needed care will be secured, rather than study participation. To avoid the stigma that surrounds having DBDs, no child will be excluded by virtue of their mental health screening status. If a child is not eligible for the study (does not evidence a DBD), the family will only be invited to attend the MFG meetings (all families in the school community will have the opportunity to attend to decrease stigma, but also enhance the functioning of all parents/families).

### Recruitment

Using the same recruitment procedures tested in our earlier studies (142, 143), we will rely on the schools and local district administration to identify participants and help with recruitment. We will make use of existing procedures at the beginning of the school academic terms during which each parent or caregiver comes to the school to meet with the administration to register their child (occurs within the first 2–4 weeks of the academic term). School administrators will give each child and parent a flyer that introduces the project and invites all the caregivers with an eligible child to contact the school for details. Community development officers and our implementing partner (RTY-Uganda) will also distribute flyers during their community visits to so that caregivers whose children meet the inclusion criteria but may not yet have reported back to school can also be informed.

Children and caregivers who indicate interest will be invited to come to the school in-person for a one-on-one information meeting with the research team, during which they will be given details of the project and will be informed, verbally and in writing, that study participation is voluntary. They will also be informed of the potential risks and benefits of participating in the program. The research team will obtain the informed consent of the primary caregiver and the assent of the child for all children. Parents will also be asked (following consent procedures) to complete screening tools for child DBDs. If the child meets the criteria for an emerging or clinically meaningful behavioral problem, they will be invited to enroll in the study and a baseline assessment will be completed prior to the start of the intervention.

### Retention and attrition

As in our previous studies (142, 143), we will ask participants to give their telephone number, and contact information for three people who will always know how to reach them, to help track their location only if we have lost contact. The research team will be in contact with all participants regularly during school roll calls to determine enrollment and attendance, as well as during the distribution and review of monthly bank statements for participants in the treatment conditions. This frequent contact will help to minimize loss to follow-up. We have effectively used these procedures in our previous research studies, resulting in very low attrition rates (7.3% over 5 years) (25, 75, 76). Based on these numbers, we conservatively expect attrition by end of follow-up to be no more than 20%.

### Ethics and informed consent

All study procedures were approved by the Washington University in St. Louis Review Board (IRB # 202202183) and by in-country local IRBs in Uganda: Uganda Virus Research Institute–UVRI (GC/127/901), and Uganda National Council of Science and Technology–UNCST (SS1205ES). Amendments to the study protocol will be submitted for approval to the above-mentioned IRBs. Participation in the *Suubi4StrongerFamilies study* will be voluntary. Written informed consent will be obtained from all participants. This will be done prior to assessment. In the consent form, it will clearly be stated that the participant can: withdraw from the study at any time, for any reason, with no explanation, and would not be penalized in any way; refuse to answer any questions at any time; review any materials and request that we erase any of their responses; make inquiries and address complaints to Secretary of the Ethics Committee at UVRI, UNCST, and Washington University in St. Louis. Participants will also be told of the potential risks and benefits of participating in the study. Each participant will receive a copy of the signed consent form.

### Study conditions

#### Economic empowerment intervention using matched savings accounts (child development account) intervention

Each child assigned to an EE group will receive a CDA held in a registered financial institution in Uganda. The child’s family members will be encouraged to contribute toward the CDA. The account will then be matched with money from the program. The maximum family contribution to be matched by the program will be an equivalent of US$10 per month per family. For children who save the maximum amount, they will have a total of $360 at the end of the intervention ($120 in savings plus $240 from the match: a 1:2 match). These amounts would be enough to pay for at least 3–4 years of a child’s upper primary educational expenses (e.g., examination registration fees, school uniforms, and any functional fees) in a public primary school. These are fees that are often prohibitive for poor school-going children to complete primary school and/or transition to secondary school to earn an ordinary level certificate that can be used to pursue advanced training or apprenticeship.

A monthly bank account statement will be generated for every child to note their accumulated savings. The statements are intended to act as “morale boosters” for the enrolled children. Also, during the intervention period, each child, with their primary caregiver as a co-signer, will have access to the money in their individual account (excluding the matching funds). In case of an emergency (for example, a family illness), participants can withdraw their own money—but not the matching funds. When the child turns 18, they will no longer need co-signers. As with our prior studies that used matching accounts (14, 19, 25, 74, 77, 143, 144), the matching funds will be kept in a separate account. To eliminate potential misuse of funds intended for education, payments from the matching fund will be made directly to the child’s school or wire transferred directly to the school’s bank account. The student will then contribute their portion of the total cost for the academic term. The same will apply to children who want to invest a portion in small business development: the check will be written to the vendors (or the wire transfer for the match will be sent directly to the vendor with the required particulars of the participant). This process is intended to eliminate the risk of family pressure on the children to withdraw money set aside for education. Participating students will be allowed to use up to 30% of their match funds to invest in a family-based income-generating activity (IGA), and the remaining 70% will be restricted only to fund the child’s education. Prior to accessing the match funds, participants will be required to complete 8 financial literacy management (FLM) workshops over a 12-month period. The in-country project coordinator will monitor the matching operations. This protocol has been successfully used in Uganda in our prior work (15, 16, 73, 76, 77, 80, 145).

The FLM workshops will consist of eight workshops that will: (a) introduce participants to the notion of asset-building; (b) cover asset-building strategies in detail, e.g., saving and investing in IGAs; and (c) cover specific topics related to saving, e.g., the importance of saving and how it can be done. As in our earlier studies, participants from the same school will be assigned to the same group during training, which will occur on weekends and school holidays.

#### The multiple family group-based family strengthening intervention

The MFG-based family strengthening approach is a hybrid of group and family interventions, rooted in several theories, including family systems theory, structural family theory, and social learning theory with elements of psychoeducation and social group work (146, 147). MFG has adopted the strengths of multiple therapeutic methods and theories to create an extremely flexible approach that has been applied to a variety of target populations struggling with a diverse range of issues (15, 16, 102, 104, 143, 145–148). MFG integrates components of existing EBPs found to successfully improve parental management and depression, mental health promoting family processes, and family strengthening (88). MFG is based on building support for parents and families by providing opportunities for parents and children to communicate in a safe setting with other families who have shared experiences (147). Advice and insight from other families is often seen as less threatening than feedback given by a therapist (147). In addition, MFG focuses on reducing stigma by normalizing shared experiences (147). Across country contexts, the family strengthening intervention is delivered in groups with multiple families present. More specifically, in the US, 6–8 families are included in each meeting. In South Africa and Uganda, 12–20 families are in attendance. At least 2 generations of a family (up to 20 families per group) are present in each session. Content and practice activities foster both within family and between family learning and interaction (149).

The MFG-based FS intervention acknowledges specific factors tied to poverty (e.g., stress) may undermine parenting (e.g., family organization, connectedness, support, and communication, and discipline practices) and contribute to poor mental health functioning (91) (see Table 1). The MFG-based FS approach will allow children and their families to share with other families in similar situations thus building hope by providing social support, normalization of similar experiences and struggles, and the sharing of effective solutions (150). The proposed study will utilize the MFG-based FS approach to specifically target family communication and supports both within and across families from the same community setting. In addition, MFG-based FS will aim to lower familial stress which may have negative impacts on children and overall family functioning. The MFG-based FS approach is an ideal way to build the protective factors of healthy parent–child relationships and communication while addressing familial, social and community stressors and barriers to children and adolescents’ mental health functioning.

**TABLE 1 T1:** MFG-based family strengthening content.

MFG target (session #)	Empirically supported family skill	MFG goals
Rules (3 and 9)	Family organization; consistent discipline	Clarify rules, consequences, rewards
Responsibility (4 nd 10)	Inter-connectedness; expectancies	Clarify responsibilities, expectations, rewards
Relationships (5 and 11)	Family warmth; within family support	Schedule for positive family interaction
Respectful communication (6 and 12)	Family communication; family conflict	Listening/talking skills (parents/children)
Stress (7 and 13)	Parenting hassles and stress; life events	Identify stressors undermining family change
Social support (8 and 14)	Social isolation	Within family and external support plan

##### Description of family strengthening intervention protocol

The protocols have been designed to provide opportunities during each session to directly apply content to the realities of family life, emergent cultural and values perspectives, as well as tailor messages to the age of the child. We have built in redundancy for missed appointments and opportunities for reinforcement. We aim for families to attend at least 7–8 meetings, as findings suggest that this dose is needed to reduce child conduct problems and the majority of families reach this goal (83, 151).

##### Program delivery

At least six facilitators per school will be trained to facilitate the delivery of both the FS and EE + MFG-based FS interventions. Parent peers and teachers will be trained separately, based on study conditions. At the end of the program, facilitators will receive a certification in child mental health competency to be offered by the Ugandan Ministry of Health.

##### Training and supervision

Training will consist of up to 6 modules. Training focuses on childhood conduct difficulties, family-level factors that have been linked to child outcomes, strategies to enhance engagement and motivation, group facilitation skills, and processes specific to family strengthening. A knowledge and skills assessment test (KSAT), to assess mastery of the content, will be administered at the end of the training (152). Facilitators will receive 2 h of supervision per month, during the intervention period.

#### Combination intervention: Economic empowerment + multiple family group-based family strengthening

The combined arm will consist of: (a) an EE intervention that comprises a family monetary savings program using CDAs (detailed above), and (b) MFG-based family strengthening intervention focused on strengthening family relationships and mental health challenges (described above) frequently faced by children growing up in low-resourced communities characterized by poverty and disease (including HIV/AIDS). Combining these interventions recognizes that children’s mental health in poverty-impacted families is directly affected by the environment in which they live, with parental communication style and perpetuation of harmful social norms within a household (and community) potentially resulting in feelings of powerlessness and low self-worth. For those reasons, we are using the MFG model to build optimism, positive thinking as well as information on how to improve family processes as a mechanism to enhance mental health functioning.

### Data collection

All assessments (see Table 2) will take place at the participant’s home, ICHAD’s field offices in Masaka or satellite sites for study collaborators, with each lasting about 60–90 min. Although we expect most participants to be English-speaking (the instructional language in all Ugandan schools), assessments will be conducted in English or Luganda (local language) depending on participants’ English proficiency. All interviewers will be fluent in English and Luganda. Questions will be translated by a certified translator. Interviewers will receive a structured and intensive training conducted by the MPIs. All questions will be interviewer-administered. We will use unannounced school visits for school attendance using the same study protocols used during our Bridges and Suubi4Her studies (R01HD070727 and R01MH113486) (23, 153, 154). During school days, we will visit schools at an undisclosed time and day to do roll calls for students enrolled in the study once every month throughout the study period.

**TABLE 2 T2:** Variables, instruments, reliability, and assessment time points.

Variable		Measurement	Reliability	Time point
**Demographics (respondent: child)**				
Age; orphan status; socioeconomic status; family stability		Socio-Demographic Questionnaire	n/a	B, 12, 24, 36

**Moderators (respondent: child)**				
Gender; orphanhood status; connections to community; utilization of religious resources				B, 12, 24, 36

**Potential mechanisms of change/mediators (respondent: child)**				
Mental health functioning	Adapted Child Depression Inventory (155)		0.65	B, 12, 24, 36
Post-traumatic stress disorder	The Child PTSD Index (156)		0.77	
Self-concept	Adapted Tennessee Self-Concept Scale (TSC-2) (25, 73, 75–78, 157)		0.81	B, 12, 24, 36
Family relations and cohesion; social support, family stability, duration of residence with family	Family Environment Scale/Family Assessment Scale (158–160)		0.54–0.87	B, 12, 24, 36
	Social Support Behaviors Scale (SS-B) (103, 161); MSPSS (74, 162)		0.69–0.84	
Stigma	Pediatric Self-Stigmatization Scale (163)		0.72–0.86	B, 12, 24, 36
Hopelessness and self-esteem	Beck Hopelessness Scale (155); Rosenberg Self-Esteem Scale (164)		0.77–0.88	B, 12, 24, 36
Food security/economic stability/assets	Household Food Insecurity Scale (165), asset ownership (166)		n/a	B, 12, 24, 36
Financial literacy and access to services	Financial literacy knowledge (167); RBA services (168)		0.80	B, 12, 24, 36
Savings (extracted from bank statements)	Monthly bank statements		n/a	B, 12, 24, 36

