Aim 2: Test the influence of EE only, MFG-based FS only, and combined EE + MFG-based FS on family financial stability (e.g., food and housing stability, material assets, and savings), parenting and protective family processes (e.g., family organization, caregiver/child interaction, cohesion, and support) and perceptions related to help seeking (e.g., stigma) on child behavioral health and functioning; and assess whether these change mechanism mediate intervention effects on DBD symptoms and behavioral functioning, and explore moderation by context-specific moderators of intervention effects;

Aim 3: Qualitatively examine participants’ experiences with each intervention arm.

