**FIGURE 1 F1:**
[figure not shown]
Study design.

We expect to involve 900 youths aged 10–14 years in primary schools, grades 5 through 7, and their adult caregivers (900) in Uganda. The selected schools will be randomized to three study conditions: (1) EE only condition with a 1:2 saving incentive match—for educational purposes and microenterprise development (*n* = 300 participants; *n* = 10 schools); (2) MFG-based FS only condition (*n* = 300 participants; *n* = 10 schools; (3) combined EE + MFG-based FS condition (*n* = 300 participants; *n* = 10 schools). There will be four data points, these include baseline (pre-test), 12, 24, and 36 months post intervention.

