#### Primary analyses for Aim 2: Evaluating the effects of the intervention on mechanisms of change

We hypothesize that: (1) H2a: Relative to participants in the MFG-based FS only group, participants in the combined EE + MFG-based FS group will have higher levels of family financial stability, parenting and protective family processes, and perceptions related to help seeking following the intervention; and (2) H2b: Relative to participants in the EE only group, participants in the combined EE + MFG-based FS group will have higher levels of family financial stability, parenting and protective family processes, and perceptions related to help seeking following the intervention. To test hypotheses H2a–H2b for mechanisms of change (e.g., asset ownership scale and food security) we will fit LMMs using the same fixed effects (study arm, time, and study arm-by-time interaction) and random effects for the school (random intercepts) and person levels (random intercepts, random slopes, and their covariance) as in the proposed H1 analyses described above. To test H2a–H2b we will perform two time-averaged comparisons of repeatedly measured observations of financial stability, parenting and protective family processes, and perceptions related to help seeking at α = 0.025 per comparison.

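### Savings is part of family financial stability, but its only listed source exists in the two EE arms alone, so contrasts with FS-only cannot be made on it

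*Protocol article*

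**What the plan says.** **Construct.** Aim 2 in the Introduction refers to "family financial stability (e.g., food and housing stability, material assets, and savings)". The opening of Methods repeats this list.

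**Source.** Table 2, under potential mechanisms of change/mediators, has a separate row, "Savings (extracted from bank statements)". Monthly bank statements are the only instrument, and the time points are baseline, 12, 24 and 36 months.

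**Who has an account.** The section on the EE intervention says "Each child assigned to an EE group will receive a CDA held in a registered financial institution in Uganda". The same section adds "A monthly bank account statement will be generated for every child to note their accumulated savings". The combined arm includes "an EE intervention that comprises a family monetary savings program using CDAs". The other single-intervention arm is listed in Methods as "2) MFG-based FS only condition (*n* = 300 participants; *n* = 10 schools", and the description of the MFG-based programme mentions no account.

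**Analysis.** H2a takes FS-only as the reference and states that "participants in the combined EE + MFG-based FS group will have higher levels of family financial stability", among other mechanisms. It is tested at α = 0.025. The mediation section uses financial stability at 12 and 24 months as a mediator of arm effects on outcomes at 24 and 36 months. The exploratory Aim 2 section repeats the comparison and the mediation for EE-only versus FS-only at α = 0.05.

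**The concern.** The measure of savings is produced by one of the interventions being compared. Children in FS-only are given no account, so they have no statements from which savings could be extracted. H2a nevertheless compares the combined arm with FS-only on a construct that names savings.

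If the plan is followed as written, H2a on savings has two possible outcomes. It may not be estimable, because one arm has no data. Or, if no statement is read as no savings, it gives a near-certain positive result that shows only that accounts were opened and used. Neither says whether households in the combined arm save more than households in FS-only. A mediation analysis that passes through this variable has the same weakness. The gap cannot be repaired at analysis, because savings not asked about in FS-only, at baseline especially, cannot be collected later.

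**Working it through.** **Step 1: the plan's own savings figure.** $10 per month × 12 months = $120 of matched family savings. The 1:2 match adds 2 × $120 = $240, and $120 + $240 = $360. This reproduces the stated maximum. It describes a CDA, so it applies only to arms that hold one.

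**Step 2: where the measure can exist.**

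| Arm | Children | CDA described | Statement-based savings |
|---|---|---|---|
| EE only | 300 | yes | possible |
| Combined EE + MFG-based FS | 300 | yes | possible |
| MFG-based FS only | 300 | no | none |

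Total: 300 + 300 = 600 of 900 children, and 0 of 300 in FS-only.

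**Step 3: which contrasts need the empty arm.**

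- H2a (combined vs FS-only): affected, for savings.
- Exploratory EE-only vs FS-only: affected, for savings.
- Mediation through savings in either of those contrasts: affected.
- H2b (combined vs EE-only): not affected, since both arms hold CDAs.

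**Step 4: FS-only coded as missing.** There is no observed FS-only value at any visit. The FS-only mean in the mixed model, and hence the H2a contrast on savings, has no data behind it. Maximum likelihood or multiple imputation could supply one only by borrowing from the CDA arms.

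**Step 5: FS-only coded as zero.** Let p be the share of combined-arm families that deposit and m the mean amount among depositors. The contrast is p × m − 0, which is positive for any p above zero, whatever the true household savings in FS-only.

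How soon would this reach significance? As an illustration, take 900 × 0.8 = 720 analysed children, so 240 per arm and 24 per school in 10 schools. FS-only is fixed at zero, and school means are compared by a t-test at two-sided α = 0.025, with 2,000 simulated trials per setting. Two inputs are assumptions that the article does not give: an intracluster correlation of 0.05 for uptake, and depositors' amounts uniform on $1 to $120 (mean $60.50).

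| Uptake p | Contrast p × $60.50 | Share of trials significant |
|---|---|---|
| 2% | $1.21 | 4% |
| 5% | $3.03 | 46% |
| 10% | $6.05 | 91% |
| 30% | $18.15 | 100% |

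The share was also 100% at 50% and 80% uptake. This is a simpler test than the planned three-level model. It shows only how little uptake is needed.

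**Step 6: mediation.** The arm-to-savings path is the contrast in Step 5. The savings-to-outcome path can be estimated only within the CDA arms, because savings does not vary in FS-only. The two arms overlap only at zero, among CDA families that never deposit. An indirect effect therefore needs one of two things. Either the slope from the CDA arms is carried over to FS-only, or self-selected non-depositors stand in for children who had no account. Both are extrapolation.

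**The case against.** The best case for the plan is about scope.

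- Savings is one example within financial stability. The H2 analysis text gives other examples, asset ownership and food security, and Table 2 restricts neither to an arm. Table 2 also lists mechanisms that H2 does not name, so a row there does not prove that savings will be tested in H2a. The full protocol or analysis plan may assign measures to contrasts. This stands as a limit on reach. It does not remove the conflict, because Aim 2 names savings in the construct and Table 2 fixes a source that one arm lacks.
- The asset or financial-services instrument may already contain a savings item. That cannot be seen in the article. If so, the remedy is to name that item.
- The section on retention speaks of "distribution and review of monthly bank statements for participants in the treatment conditions", and all three arms are active. The phrase is undefined, but it gives FS-only children no account. The line about statements for every child belongs to the EE description.

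A reader might also infer more than the article supports:

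- *Balances after 12 months reflect pay-out.* The article does not say whether savings is scored as a balance or as deposits. Monthly statements allow either, and matching funds are held separately.
- *The empty baseline biases the comparisons.* No CDA statement can exist before the intervention, so the baseline entry cannot be filled from that source. But the planned contrasts are averaged over post-intervention visits, and none is biased by this.
- *Savings will be imputed for FS-only.* The plan says that incomplete data are handled by maximum likelihood and multiple imputation. It does not say this extends to children who never had an account.

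**Conclusion.** The point holds for savings alone. Statement-based savings is structurally absent for 300 of 900 children, the whole reference arm of H2a. On that measure, H2a and EE-only versus FS-only are either not estimable or, with zeros, positive whenever any family deposits. Under the assumptions stated above, 10% uptake already gives significance in 91% of simulated trials.

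It would be tempting to say that H2a fails, or that mediation is true by construction. Neither follows. H2a on food security and asset ownership stands, as do H2b and both primary outcomes. Within mediation, only the arm-to-savings path is fixed by design. The indirect effect is better described as not identified without extrapolation, since deposits vary among families in the CDA arms.

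The conclusion rests on two readings of the article: that no account is provided outside the EE arms, and that no savings item common to all arms is named. The simulated percentages are illustrative, and the conclusion does not depend on them.

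**What to change.** 1. In Table 2 and the Aim 2 analysis text, restrict bank-statement savings to combined versus EE-only (H2b) and to describing uptake in the two CDA arms. State that it is neither imputed nor set to zero for FS-only.
2. For H2a, EE-only versus FS-only and all mediation, use one household-savings interview item asked identically in all three arms at baseline, 12, 24 and 36 months. If the asset or services instrument already has such an item, name it.
3. If no common item can be added, leave savings out of those contrasts and say so.

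The cost is a wording change and one or two questions in an interview already planned at 60–90 minutes. Self-reported savings will be noisier than bank records, but it measures the same thing in every arm.
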